### Setting

Timor-Leste is placed 133rd out of 187 countries on the Human Development Index [51], with 31.5% of the population living in severe poverty and a further 21.4% living in near poverty [51]. Over 50% of children under 5 years of age suffer from stunting, indicating chronic malnutrition [52]. A national survey in 2012 showed an overall STH prevalence of 29% in school-aged children in Timor-Leste, with 26 and 30% prevalence in the Manufahi and Aileu municipalities, respectively [53].

Open defecation in rural communities poses significant health risks. In 2015, 73% of the rural households in Timor-Leste did not have access to improved sanitation facilities, and 39% did not have access to improved water supplies [54]. Furthermore, a UNICEF survey in 2011 reported that 35% of the primary schools in Timor-Leste did not have latrines, and 62% of schools did not have regular access to a water supply [55].

Improved water and sanitation facilities across rural areas of Timor-Leste has been highlighted as a priority by the government of Timor-Leste [56], and multiple non-governmental organisations (NGOs) are also working in Timor-Leste to provide rural communities with improved access to reliable protected water sources and sanitation facilities and to promote hygiene behaviour [57–61].

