### Study outcomes

The primary outcomes will be used to examine feasibility and acceptability (objective 1). Primary outcomes relating to study feasibility and acceptability in terms of recruitment and participation (objective 1A) are as follows: the proportion of eligible children whose parents provide informed consent; the proportion of eligible children who provide stool samples, complete questionnaires and undergo measurement of height, weight and haemoglobin; and the retention rate of participants between baseline and follow-up.

Primary outcomes relating to the feasibility and acceptability of the WASH and deworming programmes (objective 1B) are as follows: the proportion of children and eligible community members who receive albendazole; the time taken for the completion of the school WASH programmes in each study cluster; the time taken to achieve 80% household latrine coverage in each intervention cluster; the proportion of schools and households with latrines and access to a reliable source of improved water; the proportion of schools with handwashing stations; and the proportion of children who report using latrines and handwashing stations.

Secondary outcomes, which will be used to inform sample size calculation (objective 1D) and to examine the study hypothesis (objective 2), are as follows: 6-month cumulative incidence of infection with STH (*Ascaris* spp., *N. americanus*, *Ancylostoma* spp. and *T. trichiura*) at follow-up; mean intensity of STH infection (measured as average number of eggs per gramme of faeces) at follow-up; mean haemoglobin concentration; and four anthropometric indices: weight-for-age, height-for-age, weight-for-height and body mass index (BMI)-for-age *Z*-scores (to identify underweight, stunting, wasting and thinness, respectively). Cumulative incidence of STH infection is the planned primary outcome in the full-scale trial. It should be noted that the term “cumulative incidence” is used for simplicity, as cases diagnosed at follow-up will include both incident infections and prevalent infections not cured by albendazole, particularly in the case of hookworm and *T. trichiura* infections [65].

All outcomes (see Table 1) will be compared between control and intervention clusters.

**Table 1 Tab1:** Study outcomes

Primary outcomes	
Proportion of eligible children who:	Provide parental informed consent
	Provide stool samples
	Complete questionnaires
	Undergo measurement of height, weight and haemoglobin

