### Analysis

For the primary outcomes, analyses will be mainly descriptive. The proportions of eligible participants who gave informed consent and participated in each aspect of data collection will be calculated (with 95% confidence intervals (CIs)) and compared across the two study arms, at both baseline and follow-up, and will also be examined separately by gender and age group. The proportion of baseline participants retained at follow-up will also be calculated and compared across the study arms. Descriptive statistics will be used to examine the completeness of data collected using the study questionnaires.

The proportion of children and eligible community members who received albendazole, the proportion of schools and households with access to various WASH components and the proportion of children who report using various WASH components will be calculated (with 95% CIs) and compared across the two study arms, at both baseline and follow-up. The time taken to complete the school and community WASH programmes will be examined using descriptive statistics (mean, median, range).

For the secondary outcomes, prevalence at baseline and cumulative incidence at follow-up will be calculated (with 95% CIs) for each STH as will the mean and standard deviation of the infection intensity, expressed as eggs per gramme of faeces. Mean and standard deviation of the haemoglobin concentration and *Z*-scores for the four anthropometric indices will also be calculated. These outcomes will be compared across both arms of the trial using mixed effects multivariable regression models that account for clustering of participants within schools and villages. Cumulative incidence of infection will be modelled using multivariable Bernoulli logistic regression, with age and sex entered as covariates, baseline infection status as a fixed effect, and school and village as random effects. The study arm will be entered as a binary fixed effect to estimate differences in cumulative incidence between the study arms, using a cumulative incidence ratio (CIR). Intensity of infection will also be modelled with random and fixed effects as described above. Mixed effects linear regression will be used to model anthropometric *Z*-scores and mean haemoglobin concentration. Stata software will be used for all analyses (StataCorp LP, College Station, TX).

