## Discussion

The current WHO guidelines for STH control focuses strongly on school- and preschool-aged children, who experience the highest burden of disease-related morbidity. In the context of significant global interest in the control of neglected tropical diseases, including significant donations from pharmaceutical companies, and recognition of the potential added benefit of WASH interventions for sustainable control, there is increasing interest in the optimal control strategies for STH.

The (S)WASH-D for Worms pilot study primarily represents a feasibility study in preparation for a cluster-randomised controlled trial (RCT) investigating the differential impact of school- and community-based integrated STH control programmes. The integrated control programme implemented in the study includes both deworming medications, distributed by the research team, and a water, sanitation and hygiene intervention, implemented by partner NGOs. The pilot study will provide an indication of the rate of recruitment and participation which could be expected in a full-scale RCT, which will be used to inform sample size calculations for the full-scale trial. The pilot study will also provide an opportunity to test the study procedures and data collection forms and to examine the feasibility and acceptability of the deworming and WASH programmes, in particular, the time frames for completion of the WASH programmes and their ability to achieve improved WASH access and use. Furthermore, it will allow for the identification of operational challenges involved in implementing such a trial in a developing country. In particular, the pilot study will give an estimation of the time frames required for the completion of the school- and community-based WASH interventions.

The pilot study sample size does not allow sufficient power to detect significant differences in secondary outcomes between study arms. Initial estimates of the secondary outcomes obtained in this pilot study will be used to provide preliminary evidence for our study hypothesis that a community-wide intervention is more effective at reducing STH infections in children than a school-based intervention and to inform sample size calculation. Results of hypothesis testing will be interpreted with caution; emphasis will be given to confidence intervals, rather than *p* values, and results will be presented in terms of assessment of “proof of principle”, rather than establishment of causation.

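### The model for infection yields a conditional odds ratio, but the arm effect is to be reported as a cumulative incidence ratio, and no conversion is stated

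*Protocol article*

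**What the plan says.** The Analysis section states both the model and the effect measure for infection. The model: "Cumulative incidence of infection will be modelled using multivariable Bernoulli logistic regression". Its other terms are fixed effects for the child's age, sex and infection at baseline, plus random intercepts for school and village. Study arm goes into the same model as a fixed term, and its purpose is "to estimate differences in cumulative incidence between the study arms, using a cumulative incidence ratio (CIR". The abbreviation list expands CIR as a cumulative incidence ratio, so it is not shorthand for an odds ratio. For this comparison the article mentions no odds ratio, no log link, no modified Poisson model and no averaging of predicted risks.

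On frequency, the Setting section reports: "A national survey in 2012 showed an overall STH prevalence of 29% in school-aged children in Timor-Leste". For the two study municipalities it gives 26% (Manufahi) and 30% (Aileu). On use, the Study outcomes section introduces the secondary outcomes as ones "which will be used to inform sample size calculation (objective 1D) and to examine the study hypothesis (objective 2", and adds: "Cumulative incidence of STH infection is the planned primary outcome in the full-scale trial".

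**The concern.** A logit link makes the arm coefficient a difference in log odds, so its exponent is an odds ratio. With random intercepts for school and village, and with age, sex and baseline infection in the model, that odds ratio is also conditional: it compares children with the same covariates and the same cluster effect. A CIR compares average risks. The two nearly agree when infection is rare. Otherwise the odds ratio lies further from 1, whichever arm does better.

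This goes beyond a detail left out for brevity. The article chose to name the model and the measure, and as named they do not match. An analyst following the text literally could exponentiate the arm term and label it a CIR. The estimate, and the confidence interval on which the Discussion places its emphasis, would then overstate the relative reduction in an outcome intended as primary in the full trial.

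**Working it through.** The article states no effect size, sample size or power on this point, so there is no figure of the plan's own to reproduce. The check is how far an odds ratio departs from the CIR it would be taken for.

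**Inputs.** Control risk p0: 26%, 29% and 30% from the Setting section, used only as a proxy because they are prevalences of any STH; 5%, 10%, 45% and 60% are assumed, to show the range. True CIR: 0.50, 0.67 and 0.70, all assumed.

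**Step 1: unadjusted odds ratio.** With p1 = CIR × p0,

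OR = [p1/(1 − p1)] / [p0/(1 − p0)] = CIR × (1 − p0) / (1 − CIR × p0).

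Example: p0 = 0.29 and CIR = 0.67 give p1 = 0.1943 and OR = 0.67 × 0.71 / 0.8057 = 0.590.

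| Control risk | CIR 0.50 reads as | CIR 0.67 reads as | CIR 0.70 reads as |
|---|---|---|---|
| 5% | 0.487 | 0.659 | 0.689 |
| 10% | 0.474 | 0.646 | 0.677 |
| 26% | 0.425 | 0.600 | 0.633 |
| 29% | 0.415 | 0.590 | 0.624 |
| 30% | 0.412 | 0.587 | 0.620 |
| 45% | 0.355 | 0.528 | 0.562 |
| 60% | 0.286 | 0.448 | 0.483 |

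At 29-30%, a 33% reduction would read as about 41%, and a 50% reduction as about 59%. At 5-10%, a 30% reduction would read as 31-32%.

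**Step 2: the reverse direction.** CIR = OR / (1 − p0 + p0 × OR). An odds ratio of 0.50 corresponds to a CIR of 0.51 at 5% risk, 0.53 at 10%, 0.575 at 26%, 0.585 at 29% and 0.71 at 60%.

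**Step 3: effect of conditioning.** The planned model is conditional, so Step 1 slightly understates the gap. Assume p0 = 0.29, 29% infected at baseline, an odds ratio of 4 for baseline infection, and a normal random intercept with SD 0, 0.5 or 1.0 on the logit scale. Solving numerically for the conditional odds ratio that gives a marginal CIR of 0.70 yields 0.597, 0.586 and 0.556. For a marginal CIR of 0.50 it yields 0.386, 0.373 and 0.340.

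**Step 4: sample size, only if the ratio is carried forward as a risk ratio.** Take p0 = 0.29, a true CIR of 0.70, two-sided 5%, 80% power, individual-level formula, no design effect: n per arm = (1.96 + 0.8416)² × [p0(1 − p0) + p1(1 − p1)] / (p0 − p1)².

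- True p1 = 0.203: 7.849 × 0.3677 / 0.00757 ≈ 381.
- p1 = 0.29 × 0.624 ≈ 0.181: about 233. With that number, power against the true effect is about 59%.

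**The case against.** The strongest reply is that the text never says the coefficient will be exponentiated and called a CIR. A ratio of risks can be obtained from a logistic model by standardising predicted risks, Stata is named for all analyses, and a short article may leave that step to a fuller document. This stands in part: a reader might infer that the reported effect will certainly be overstated, and the article does not support that. What remains is that the measure named is not the one the named model yields directly, and nothing connects them.

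Second, a reader might take 26-30% as the risk for this outcome. It is not. It is any-STH prevalence from a 2012 survey, whereas the outcomes are defined per species and measured six months after observed albendazole. No species-specific follow-up risk is given. A single species could be well below 26-30%; reinfection or PCR detection could push the risk up. This objection stands in full, which is why the range is shown.

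Third, a reader might infer that the full trial will be too small. The article does not say so. Objective 1D in the Background names prevalence, intensity and nutritional estimates as the sample-size inputs, and the Analysis section calculates cumulative incidence for each species directly, so usable risks exist whatever the model reports. Step 4 is therefore conditional.

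Fourth, the Discussion concedes: "The pilot study sample size does not allow sufficient power to detect significant differences in secondary outcomes between study arms". To illustrate, 522 children in 6 clusters average 87 per cluster. With an assumed intracluster correlation of 0.05 the design effect is 1 + 86 × 0.05 = 5.3, leaving about 49 effective children per arm. At 29% control risk, a CIR of 0.67 then has an approximate 95% interval of 0.33 to 1.38. A shift from 0.67 to 0.59 is small beside that. This limits the severity; it does not make the label correct.

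**Conclusion.** The mismatch is in the text and should be corrected. The model as described yields a conditional odds ratio, the reported measure is a ratio of risks, and no conversion is given. The size of any distortion depends on two things the article does not settle: whether the raw coefficient is what gets reported, and the control risk for each species at follow-up. If the coefficient is reported and the risk is near 29-30%, 0.67 reads as about 0.59 and 0.50 as about 0.41, or somewhat further from 1 once conditioning is allowed for. At 5-10% risk the distortion is negligible.

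The proof-of-principle reading could be misled, and the sample size of the full trial only if the ratio is used there as a risk ratio. For a secondary outcome in a non-randomised pilot of six clusters, declared underpowered and read through its confidence intervals, the severity is moderate to minor. No decision within the pilot turns on it.

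**What to change.** Add one sentence to the Analysis section. The preferred version keeps the logistic model and obtains the CIR by marginal standardisation: predict each child's risk with arm set to control and then to intervention, averaging over the random effects; take the mean of each; and report the ratio and the risk difference, with intervals that respect the six clusters. The minimal version is to call the exponentiated coefficient an odds ratio and present it beside the observed cumulative incidences by arm.

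A modified Poisson model would give a risk ratio directly, but its school-level robust variance is unreliable with six clusters and should not be used without a small-sample correction.

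Whichever version is chosen, any effect taken into the full trial's sample size should be stated as a pair of risks or as a ratio whose type is named. The cost is a sentence and one post-estimation step, with no new data. Where infection is common, the reported effect will look somewhat less favourable than the raw coefficient.

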## Methods

### Design

This pilot study is a two-arm, non-randomised cluster intervention study. The six participating clusters, each based around a local primary school, are located in Aileu and Manufahi municipalities of Timor-Leste. Three clusters comprise the “control” arm of the study: in these, a WASH programme is delivered to the primary school, and albendazole is distributed to the schoolchildren. The other three clusters comprise the “intervention” arm, in which a WASH programme is delivered to both the primary school and the community in which the school is located, and albendazole is distributed to all community members. The follow-up period for the pilot study is 6 months following the distribution of albendazole, which will allow sufficient time for STH reinfection to occur [24], and represents the follow-up interval planned for the full-scale trial, which will take place over a 2-year period. Figure 1 depicts a flow diagram for the pilot study. This pilot study is registered with the Australian New Zealand Clinical Trials Registry (registration number ACTRN12615001012561).

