### Selection and recruitment of clusters

Because each of the two partner NGOs only had capacity to conduct the WASH programme in one of the study arms within the required study time frame, and operated in neighbouring but different administrative areas, a randomised design could not be used for the pilot project. In the full-scale study, the intention is to randomise communities to the intervention and control arms.

For the pilot study, communities were considered eligible if they contained a primary school which was suitable for a school-based WASH programme (i.e. did not have access to functional improved latrines) and were located in a village with low sanitation coverage (i.e. less than 50% of households with latrines). Communities were selected in consultation with the implementing partner NGOs, based on their upcoming activities which fit into the study time frame.

Members of the (S)WASH-D for Worms research team accompanied NGO staff to community meetings in each cluster. For intervention communities, this occurred at the community “triggering”, and for control communities, this was a pre-arranged meeting with community and school leaders to explain plans for the school-based WASH programme. In all clusters, the study was explained to the village leader and head of school, who provided consent for the study activities to take place in their community. During the triggering in intervention communities, trial staff were also given the opportunity to explain the research study to the community. Following these initial meetings, plans were made for the research team to return for baseline data collection at the schools, within 1 to 3 weeks of the first meeting and prior to the commencement of the WASH programme.

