#### Stool samples

Stool samples are collected at both baseline and 6-month follow-up. On the first day of each field visit, all participating children are given an explanation of the study and requested to provide a stool sample as part of their participation. Each child is given a labelled plastic container and provided with instructions on the collection of a faecal sample, ideally to be done the following morning and returned to the field team at the school.

Upon receipt of the stool specimens by the field team, two aliquots of 2–3 g are taken and preserved in 15-mL centrifuge tubes—one containing 8 mL of 10% formalin, and the other containing 5 mL of 5% potassium dichromate.

The formalin-fixed samples are transported to the University of Melbourne, Victoria, Australia, for diagnostic processing using microscopy. This is achieved using a simple sodium nitrate flotation technique and direct microscopy to quantify the number of STH eggs (*A. lumbricoides*, hookworm spp. and *T. trichiura*) in each faecal sample [66].

The potassium dichromate-fixed samples are sent to the QIMR Berghofer Medical Research Institute, Brisbane, Australia, for diagnostic processing using a polymerase chain reaction (PCR) technique. DNA is extracted using the PowerSoil DNA extraction kit, with modifications [67], and a real-time multiplex PCR is then undertaken to detect and quantify soil-transmitted helminths (*Ascaris* spp., *N. americanus*, *Ancylostoma* spp. and *T. trichiura*) [68].

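### The infection-intensity model adjusts for yes/no baseline infection but not for the measured baseline egg count, so a difference in burden among infected children could enter the arm effect

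*Protocol article*

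**What the plan says.** The Analysis section specifies the logistic model for cumulative incidence "with age and sex entered as covariates, baseline infection status as a fixed effect, and school and village as random effects", plus study arm as a binary fixed effect. For intensity it gives no separate list of terms: "Intensity of infection will also be modelled with random and fixed effects as described above". Read together, the intensity model contains arm, age, sex, baseline infection status, and random effects for school and village.

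Three other places bear on this:

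- **Outcome.** Study outcomes lists as secondary "mean intensity of STH infection (measured as average number of eggs per gramme of faeces) at follow-up". The secondary outcomes serve the sample size calculation (objective 1D) and the study hypothesis (objective 2).
- **Baseline data.** Under Stool samples, "Stool samples are collected at both baseline and 6-month follow-up", and the formalin-fixed samples undergo "direct microscopy to quantify the number of STH eggs". A second aliquot goes to a PCR that both detects and quantifies.
- **Allocation.** Design states: "This pilot study is a two-arm, non-randomised cluster intervention study". Selection and recruitment of clusters explains that each NGO could serve only one arm and that the two "operated in neighbouring but different administrative areas, a randomised design could not be used for the pilot project".

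**The concern.** The baseline value of the intensity outcome is measured, yet the model reduces it to infected or not infected. A child with a light infection and a child with a heavy one receive the same adjustment.

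In a randomised trial this would mainly cost precision. Here arm coincides with NGO and area, with three clusters on each side, so baseline balance cannot be presumed, and similar prevalence does not imply similar egg counts among infected children. The random effects do not help: arm is constant within a school or village, so a difference between arms loads on the arm term.

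The protocol makes carry-over plausible. Study outcomes notes that cases found at follow-up will include infections that the drug failed to clear, especially hookworm and *T. trichiura*. At stake is the intensity estimate used as preliminary evidence for the hypothesis.

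**Working it through.** The plan states no effect size, power or baseline-to-follow-up correlation for intensity, so there is no figure of its own to reproduce. The check asks how large a false arm effect could be when the true ratio is 1.

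**Inputs from the protocol.** Prevalence 29% (Setting; national, any STH, 2012 survey). Consented children: 522 (Participants).

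**Assumed inputs.** Equal baseline prevalence in both arms. Infected control children have twice the egg count of infected intervention children, a log difference of ln 2 = 0.693. Correlation *r* between baseline and follow-up log count among infected children is 0.3, 0.5 or 0.7, with equal standard deviations, so the slope equals *r*.

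**Formula.** Given infection status, the false arm difference is *r* × ln 2 among infected children and 0 among uninfected children. The model has one arm term, so with equal prevalence it averages these in proportion to prevalence *p*:

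log bias ≈ −*p* × *r* × ln 2.

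If only a share *s* of infected children stays positive after albendazole, unrelated to baseline count, multiply by *s*. The last two columns show the effect of halving prevalence (0.29 / 2 = 0.145) and of an assumed *s* = 0.4.

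| *r* | *p* = 0.29 | *p* = 0.145 | *p* = 0.29, *s* = 0.4 |
|---|---|---|---|
| 0.3 | −0.060, ratio 0.94 | −0.030, ratio 0.97 | −0.024, ratio 0.98 |
| 0.5 | −0.101, ratio 0.90 | −0.050, ratio 0.95 | −0.040, ratio 0.96 |
| 0.7 | −0.141, ratio 0.87 | −0.070, ratio 0.93 | −0.056, ratio 0.95 |

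Example: 0.29 × 0.5 × 0.693 = 0.101 and exp(−0.101) = 0.90. If the heavier burden lay in the intervention arm, the ratios would invert (1/0.94 = 1.06 to 1/0.87 = 1.15) and could mask a benefit.

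**Second check, on the count scale.** Negative binomial models were fitted to simulated data: 200 runs per setting, 522/2 = 261 children per arm (equal split assumed), true arm ratio 1.00, no cluster effects. The elasticity *b* of follow-up count on baseline count among infected children is assumed.

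| Prevalence | Baseline difference | *b* | Status only | With log baseline count |
|---|---|---|---|---|
| 30% | twofold | 0.3 | 0.96 | 1.02 |
| 30% | twofold | 0.6 | 0.87 | 0.99 |
| 30% | threefold | 0.3 | 0.90 | 1.00 |
| 30% | threefold | 0.6 | 0.82 | 1.00 |
| 60% | twofold | 0.3 | 0.89 | 1.01 |
| 60% | twofold | 0.6 | 0.79 | 1.00 |
| 60% | threefold | 0.3 | 0.82 | 0.99 |
| 60% | threefold | 0.6 | 0.66 | 0.98 |

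With no baseline difference, or with *b* = 0, both models gave 0.99 to 1.02. Both conditions are therefore needed for bias. The 60% rows have no source in the protocol and show only how the bias grows with prevalence.

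**The case against.** The strongest reply is that the consequence is limited and the harm hypothetical. Most of this stands.

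- **Not all burden differences pass through.** A reader might infer that any pre-existing difference in worm burden ends up in the arm effect. It does not: status adjustment already takes out the part due to prevalence. What remains needs both a difference among infected children and carry-over after directly observed treatment. The protocol shows neither, and Setting reports only similar municipal prevalences (26% and 30%).
- **The 29% is generous.** It is prevalence of any STH, whereas outcomes are analysed by species, so on that survey it is a ceiling for any single one. Background also describes albendazole as acting quickly on *Ascaris* and hookworm, which weakens carry-over.
- **Sample size.** A reader might infer that a larger residual variance would be passed to the sample size calculation for the full trial. Nothing in the protocol says so. Analysis calculates the mean and standard deviation of intensity directly, which the covariates do not affect, and the planned primary outcome of the full trial is cumulative incidence.
- **Cautious interpretation.** Intensity is secondary in a pilot that Discussion admits is underpowered and will read without causal claims. This tempers the conclusions but does not correct the estimate: the confidence intervals that Discussion emphasises would be centred on the same biased value.
- **Left to an analysis plan.** The distribution and transformation reasonably are. The covariate set is not, because the protocol fixes it by back-reference. If an analysis plan already adds baseline counts, only the sentence needs aligning.

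**Conclusion.** The point holds in limited form. As written, the intensity model uses yes/no baseline infection and leaves out a baseline count that the study collects, in a design where baseline balance between arms cannot be assumed. A difference in egg count among infected children that persists to follow-up would be read as an arm effect.

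The size is unknown. A false ratio of about 0.94 to 0.87 rests on a twofold baseline difference, correlation 0.3 to 0.7, 29% prevalence and no true effect; lower species prevalence or high cure moves it towards 1. With three clusters per arm, ordinary variation between clusters may well exceed a bias of this size.

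Nor should the reader infer that adding the baseline count would make the arms comparable. Other differences tied to NGO and area would remain. This is an inexpensive improvement to a secondary analysis and does not invalidate the pilot.

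**What to change.** In the intensity model, keep arm, age, sex, baseline infection status and the random effects, and add the child's baseline intensity on the same measure as the outcome:

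- for *Ascaris*, *T. trichiura* and pooled hookworm, for example log(baseline eggs per gramme + 1) from microscopy;
- where *N. americanus* and *Ancylostoma* are analysed separately, the baseline PCR quantity, because microscopy counts hookworm only as a group and gives no baseline egg count for each.

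Report the model with status alone as a sensitivity analysis.

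The cost is one extra parameter per model and a changed sentence in Analysis. No extra samples or visits are needed, since both laboratory methods are already planned for the baseline stool. Children first enrolled at follow-up have no baseline value under either model, so the change does not worsen that gap.
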